#### Childbirth Experience Questionnaire

The Childbirth Experience Questionnaire (CEQ) was developed in 2010 to measure the impact of an intervention on a woman’s childbirth experience. It includes four main aspects of the experience: own capacity, professional support, perceived safety and participation.

In COPE, participants will complete the UK-validated CEQ via an electronic, telephone or paper questionnaire within 4 weeks. On the consent form, participants will choose how they would prefer to complete the questionnaire and provide contact details as required.

#### Health economics assessments

Resource use will be based on:

Entries made in designated sections of participants’ electronic case report forms (eCRFs). The eCRFs will be used to record data on procedures (surgical) and interventions (including units of blood products transfused) and dates of patient admission and discharge. This will be collected before discharge.A resource use questionnaire (electronic, telephone or paper) will be administered at the 4-week follow-up, with a telephone reminder if no response is received within 2 weeks. The participant’s choice of how they would prefer to complete the questionnaire will be recorded on the consent form.Hospital Episode Statistics data sourced from NHS England Digital (for participants recruited in England). Data will be requested pertaining to outpatient, inpatient, critical care and emergency department attendances from 3 months prior to randomisation to 4 weeks postrandomisation (following completion of follow-up).

Unit costs will be obtained from NHS reference costs and other standard NHS sources.

Quality-adjusted life-years (QALYs) will be estimated from utilities derived from trial participant responses to EuroQol quality of life questionnaires (EQ-5D-5L) (and applying recommended methods for generating UK-relevant utilities) administered for completion at 24 hours and at 4 weeks postrandomisation. The participants will choose how they would prefer to complete the questionnaire on the consent form.

### Mixed-methods substudy

During the first 13 months of recruitment, women and birth partners’ views and experiences of recruitment and RWPC in COPE will be explored using postrandomisation questionnaires, recorded recruitment discussions and semistructured interviews. All women and birth partners included in COPE are eligible, including those who decline use of data and follow-up. The postrandomisation questionnaire and interviews (conducted within a month of recruitment) will explore: COPE information provision, approaches to recruitment, decision-making, willingness to participate and views on trial acceptability. Audio recorded trial consent discussions with patients and birth partners (if applicable) will provide insight on how the trial and RWPC is communicated. Focus groups and interviews with clinical and research staff will explore the acceptability of the COPE trial, site training, screening, administering the interventions, documentation and the logistics of running the trial. Data will be collected until the point of information power^22^ is reached. Interim findings will be used to inform approaches to recruitment and consent procedures for COPE and future time-critical obstetric trials.

### Analysis plan

The primary analysis will follow the intention-to-treat principle as far as practically possible, such that all women receiving a drug intervention for PPH and for whom the outcome is known, will be included in their randomly allocated group, regardless of the intervention received. All analyses will be conducted using a 5% two-sided level of statistical significance and 95% CIs throughout.

The primary analysis will use binomial regression with treatment group and mode of birth as fixed effects, and site fitted as a random effect. While the primary analysis will include all women with an indicator for mode of delivery, secondary subgroup analyses will be presented for each mode.

The secondary outcomes will be analysed using binomial regression for binary outcomes and linear regression for continuous outcomes. The CEQ will be scored according to its manual and analysed with linear regression. A blind review will be conducted prior to the database lock to assess the appropriateness of the planned analysis methods.

Baseline characteristics will be presented using descriptive statistics only; there will be no statistical tests between randomised groups.

Adverse reactions (ARs) and serious ARs/suspected unexpected SARs will also be presented using descriptive statistics only.

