### Rationale for chosen treatments in this study

As uterine atony is the most common cause for PPH, intravenous oxytocin is universally recommended as first-line therapy. However, the recommended dosage varies. While the National Institute for Health and Care Excellence (NICE) and WHO recommend 10 international units (IUs) intravenously; the Royal College of Obstetricians and Gynaecologists guidelines and Mothers and Babies: Reducing Risk through Audits and Confidential Enquiries across the UK (MBRRACE-UK) suggest 5 IU.^4 9 10^ There are no direct comparisons of the two doses that address efficacy. Although studies suggest that 3 IU is adequate,^11 12^ we will use a higher dose in this study (5–10 IU) to prevent criticism of inadequate dosing. The risk of this is transient hypotension that occurs with rapid injection. However, this was not seen in a recent randomised controlled trial in which 517 women were given 10 IU of oxytocin as an intravenous bolus over 1 min.^13^ The need for slow intravenous injection will be emphasised in training. Women who have a caesarean section often have intravenous oxytocin prophylaxis, a spinal anaesthetic and greater blood loss due to the surgical procedure. Therefore, participants recruited following caesarean section will be given only 5 IU, which is in line with anaesthetic recommendations.

The PPH rate is increasing, and this may be partially related to the overuse of oxytocics in labour for induction and augmentation.^10^ Laboratory studies on myometrium suggest that repeated use of oxytocics leads to the saturation of oxytocin receptors and reduced efficacy of oxytocin as a therapy.^14^ Attention has, therefore, turned to prostaglandins as an alternative approach to improving the strength of uterine contractions in the event of uterine atony. Carboprost is a prostaglandin F2a analogue that is given intramuscularly. There are 13 small studies of carboprost for PPH prophylaxis; these suggest greater efficacy but also a significant rate of adverse events that may make it less tolerable for women.^15^ Carboprost is also more expensive than oxytocin. There are no studies of carboprost for PPH treatment,^16^ but NICE recommends carboprost as a treatment. NICE and others have suggested the need for a major randomised trial to ascertain both the effectiveness of carboprost and its optimal position in a PPH treatment pathway relative to other drugs such as oxytocin.^2 4^

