#### Original sample size calculation

To detect a 2.3% reduction in a 5.8% transfusion rate (relative risk 0.60) using a Fisher’s exact test with 90% power (alpha 0.05), we would require 1880 participants per group, increasing to a total of 3948 allowing for 5% loss to follow-up.

The magnitude of treatment effect for the primary outcome is needed to change long-established clinical practice and to represent a significant advantage, given the carboprost cost and side effects.

Data from sites and published literature provide a range of transfusion rates, the variation of which may be explained by the time point of randomisation. Table 1 demonstrates the impact of varying the event rate within this range on the study power, all other parameters including the relative effect size are maintained. Therefore, even if the transfusion rate was the lowest observed, the study would still have good power. However, the most relevant and accurate data are from a recent unpublished review of Liverpool data, and we based our sample size calculations accordingly.

**Table 1 T1:** Event rate and associated power

Transfusion rate (%)	Power (%)
3.5	71
4.0	77
5.8	90
7.5	96
10	99

Relative effect size 0.60, alpha=0.05, Fisher’s exact test.

It is planned to recruit equal numbers of women following caesarean and vaginal births to ensure that study results are convincing across both subgroups. This is to ensure that the study has the potential to impact clinical practice across both modes of birth. Within each subgroup, we would be able to detect a decrease in transfusion rate from 5.8% to 3.0% with 85% power (alpha=0.05, Fisher’s exact test).

Repeat uterotonic is an important secondary outcome, and this sample size will provide 87% power, using a χ^2^ test, to detect a 4.2% reduction from a control group rate of 23.7%.

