§ Postnatal (emergency pathway) consent is obtained after childbirth ideally within 24 hours or prior to discharge/transfer to another hospital. If consent is not obtained prior to discharge, the appropriate consent procedures should be followed.

¶ To be completed at 24 hours after randomisation.

** Haemoglobin (in non-transfused women only) will be ideally obtained postnatally on the day following birth (12–36 hours postbirth) or at discharge, whichever is soonest.

†† All deaths collected from the time of randomisation until hospital discharge or 4 weeks, whichever is earlier.

‡‡ Serious adverse events and serious adverse reactions will be actively monitored and reported from the time of randomisation until hospital discharge or 4 weeks, whichever comes first. Adverse reactions of particular interest will be collected on a separate single timepoint eCRF.

eCRF, electronic case report form.

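### The wording on adverse reactions points to no planned between-arm estimate and sits awkwardly with the general promise of 95% confidence intervals; a risk difference with interval for the prespecified reactions would be a cheap improvement

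*Protocol article*

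**What the plan says.** The relevant text is in the Analysis plan section of the protocol article.

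- On adverse reactions: "Adverse reactions (ARs) and serious ARs/suspected unexpected SARs will also be presented using descriptive statistics only".
- Immediately before that, on baseline data: "Baseline characteristics will be presented using descriptive statistics only; there will be no statistical tests between randomised groups". The word *also* in the first sentence refers back to this one.
- Near the start of the section, as a general rule: "All analyses will be conducted using a 5% two-sided level of statistical significance and 95% CIs throughout".
- On other outcomes: "The secondary outcomes will be analysed using binomial regression for binary outcomes and linear regression for continuous outcomes".

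Elsewhere the article explains why side effects matter to this comparison. Under Original sample size calculation, the size of the target effect is said to be needed to change established practice and "to represent a significant advantage, given the carboprost cost and side effects". Under Rationale for chosen treatments in this study, the prophylaxis trials of carboprost are said to suggest better efficacy but also "a significant rate of adverse events that may make it less tolerable for women". The Risks and benefits section puts side effects at about 15% in those trials. A footnote to Table 3 (Outcome measures) adds: "Adverse reactions of particular interest will be collected on a separate single timepoint eCRF".

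**The concern.** This is a stated method, not a detail left to a later document. An analysis plan that follows the sentence as written would tabulate counts and percentages by arm and stop there.

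The treatment given to baseline data does not carry over well. Under sound randomisation, baseline differences are due to chance, so there is nothing to estimate. Adverse reactions arise after randomisation and may be effects of treatment, so their difference between arms is a quantity of interest. The article also says there have been no studies of carboprost as a treatment for postpartum haemorrhage. On its own account, then, this double-blind trial would supply randomised evidence on harms that does not yet exist for this use.

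If only percentages appear, readers are left to judge by eye whether a difference is well established. An imprecise excess may be over-read, or a real one passed over because no comparison was planned. Efficacy, by contrast, will have a modelled estimate and an interval.

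**Working it through.** **What the sentences commit to.** The specific sentence on adverse reactions uses *only*; the general sentence promises intervals for all analyses. They can be reconciled in two ways. Either adverse reactions are outside the general rule and get no interval, or *descriptive* is meant to exclude tests and models while still allowing an interval. A specific sentence normally governs a general one, so the first reading is the natural one, but the text does not settle it.

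**Is there a figure in the plan to reproduce?** No. The article gives no rate of adverse reactions on oxytocin and no precision target for harms. The check below asks only whether an interval would be informative at the planned size.

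**Inputs.**
- Total 2000, allocated 1:1 (Sample size; Interventions and treatments): 1000 per arm.
- 1000 women per mode of birth (Sample size): 500 per arm within each mode.
- Carboprost rate of any side effect: 15%, the article's approximate figure from prophylaxis trials (Risks and benefits).
- Oxytocin rate: not given. **Assumed** at 2%, 5%, 10% and 12%.

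**Formula.** Wald 95% CI for a difference of proportions: d ± 1.96 × √[p₁(1 − p₁)/n + p₂(1 − p₂)/n].

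**Worked example, 15% v 5%, n = 1000 per arm.** Variance = 0.15 × 0.85/1000 + 0.05 × 0.95/1000 = 0.0001275 + 0.0000475 = 0.000175. The standard error is 0.01323 and the half-width 1.96 × 0.01323 = 0.0259. The difference is 10.0 points, 95% CI 7.4 to 12.6.

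| Assumed oxytocin rate | Difference (points) | 95% CI, 1000 per arm | Half-width, 1000 per arm | Half-width, 500 per arm (one mode of birth) |
|---|---|---|---|---|
| 2% | 13.0 | 10.6 to 15.4 | 2.4 | 3.4 |
| 5% | 10.0 | 7.4 to 12.6 | 2.6 | 3.7 |
| 10% | 5.0 | 2.1 to 7.9 | 2.9 | 4.1 |
| 12% | 3.0 | 0.0 to 6.0 | 3.0 | 4.2 |

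Over this range, the difference in any side effect would be estimated to within about 2.4 to 3.0 points overall.

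**Less common reactions, both rates assumed.** At 1000 per arm, 4% v 2% gives 2.0 points (0.5 to 3.5), and 3% v 2% gives 1.0 point (−0.4 to 2.4). The two pairs of percentages look much alike in a table, yet one interval excludes zero and the other does not. This shows what an interval adds; it says nothing about what the trial will find.

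**The case against.** The strongest reply has five parts.

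1. **The plan does not forbid intervals.** A reader might infer that the text rules out any treatment difference or confidence interval for harms. It does not say so. The explicit exclusion in the preceding sentence is of tests, it concerns baseline data, and the same section promises intervals for all analyses. This stands: the absence of an estimate is the natural reading, not a stated rule.
2. **There is no commitment to weigh harm against benefit.** A reader might infer that the trial binds itself to such a weighing and then fails to analyse one side. The article says only that the target effect was chosen in view of cost and side effects. Aims and objectives lists efficacy, cost-effectiveness and participants' views, and no safety objective. This stands too: no stated objective is left without an analysis.
3. **The prespecified reactions may be secondary outcomes.** In Table 3 they come below the Clinical outcomes heading, and binary secondary outcomes get binomial regression. This is possible, but the table does not establish it: the rows below that heading also include the assessment of serious adverse events and the resource use questionnaire.
4. **Tolerability is partly captured elsewhere.** Quality of life at 24 hours and 4 weeks feeds the economic analysis, and the Childbirth Experience Questionnaire is analysed by linear regression. That is true, but neither estimates the excess risk of a particular reaction, and the 24-hour questionnaire goes only to women who consent on site.
5. **Readers can compute a crude interval from the arm counts.** They can. What they would lack is a prespecified estimate adjusted for mode of birth, the stratification factor.

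Descriptive reporting of adverse reactions is also common practice. Together these points lower the weight of the concern without removing it.

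**Conclusion.** The point holds as a modest improvement. The sentence on adverse reactions, read naturally, plans no between-arm estimate for reactions that form part of the article's own case for the target effect and are collected on a dedicated form. It also sits in tension with the general sentence on confidence intervals. No number in the article is wrong on this point, and nothing here affects the primary analysis or the sample size.

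The size is illustrative only. With 1000 per arm and 15% on carboprost, assumed oxytocin rates of 5% to 10% give differences from 10.0 points (7.4 to 12.6) down to 5.0 points (2.1 to 7.9). This rests on assumed oxytocin rates, on a carboprost rate for any side effect taken from prophylaxis rather than treatment, on complete data in both arms, and on an unadjusted Wald interval. It shows that useful precision is available for common reactions. It is not evidence of an actual excess.

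**What to change.** - For each prespecified adverse reaction of particular interest, report the number and percentage by arm plus the risk difference with 95% CI, adjusted for mode of birth where counts allow. Give no p-values, and label the intervals as estimation without multiplicity control.
- Keep serious reactions and other rare reactions as descriptive listings, where an interval would add little.
- Reword the sentence on adverse reactions so that it agrees with the general rule on intervals, and say whether the reactions of particular interest count as secondary outcomes.

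The cost is a sentence or two in the plan and a few table columns, with no change to data collection. The one downside is several intervals without multiplicity control, which the label addresses.

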### Health economic analysis

Total costs from the perspective of the NHS and Personal Social Services will be combined with QALYs to calculate the incremental cost-effectiveness (utility) ratios (ICERs) of carboprost versus oxytocin. Where appropriate, missing resource use or health outcome data will be imputed. The number of QALYs experienced by each patient will be calculated as the area under the curve using the trapezoidal rule and corrected for 24-hour measurement. We will employ parametric approaches for analysing cost and QALY data that assume normal distributions given the large samples where the near-normality of sample means is approximated. Stratified cost-effectiveness analyses will be conducted on important, prespecified patient subgroups. Estimates of ICERs will be compared with the £20 000–£30 000 per QALY threshold of cost-effectiveness specified by NICE, and a range of sensitivity analyses will be conducted to assess the robustness of the analysis. The joint uncertainty in costs and benefits will be presented as cost-effectiveness acceptability curves.

A full health economics analysis plan will be completed before conducting the analysis.

### Substudy data analysis

Qualitative analysis of interviews, focus groups, audio recorded recruitment discussion data and open response questionnaire data will be interpretive and iterative^23^ using a reflexive thematic analysis approach.^23 24^ Quantitative data from the parent and staff questionnaires will be analysed using descriptive statistics. Data will then be synthesised drawing on the constant comparative approach.^25 26^

### Data Management & Trial Monitoring

Data management and trial monitoring are delegated to the LCTC. Participants will be recruited and followed up for a maximum of 4 weeks postnatally. The recruiting hospital sites will directly enter data into a secure database. Separate data management and monitoring plans, and standard operating procedures will detail the processes conducted at the LCTC in accordance with ethical and regulatory requirements, to ensure reliability and validity of the trial data.

An independent data and safety monitoring committee (IDSMC) and TSC will oversee trial progress, and the members’ signed charters are held in the Trial Master File. Formal interim analyses of the accumulating data will be performed by LCTC at regular intervals (at least annually) for review by the IDSMC. The IDSMC will be asked to give advice to the TSC and trial management group (TMG) on whether the accumulated data from the trial, together with results from other relevant trials, justifies continuing recruitment of further patients or further follow-up. A decision to discontinue recruitment, in all participants or in selected subgroups, will be made only if the result is likely to convince a broad range of clinicians including participants in the trial and the general clinical community.

### Confidentiality

Individual participant medical information obtained as a result of this study is considered confidential, and disclosure to third parties is prohibited without prior agreement in accordance with the Common Law Duty of Confidentiality. Agreement will be achieved during the trial consent process for disclosure by the clinical care staff to the COPE research team, and for sharing of information between the COPE team and NHS England Digital. Medical information may also be given to the participant’s wider medical team and all appropriate medical personnel responsible for the participant’s welfare.

Data processing will be performed in accordance with applicable data protection legislation. The University of Liverpool and Bangor University are registered with the Information Commissioner’s Office; as Data Controllers for this study, they will process data under the legal basis of performing a task in the public interest for research purposes.

The LCTC will be undertaking activities requiring the transfer of personal identifiers (eg, name):

Verification that appropriate informed consent for trial participation is obtained will be enabled by the provision of copies of participants’ signed informed consent forms to the LCTC by recruiting centres. This requires the transfer of name data to the LCTC.Obtaining medical data from NHS England Digital will require LCTC to collect NHS numbers and transfer them to the applicable organisations.

This transfer of identifiable data is disclosed in the patient information sheet.

## Ethics and dissemination

The study is conducted in accordance with the World Medical Association Declaration of Helsinki (1996) and has been approved by Coventry and Warwickshire Research Ethics Committee (REC) (18/WM/0227) and Health Research Authority (HRA). The current protocol is version 8.0 (6 March 2024).

Two key potential ethical issues were identified in COPE, and our approach to addressing them during the study design stage was informed by our patient and public involvement (PPI) activities. These two issues are the consent process and the administration of a placebo injection along with the active treatment injection.

The ethics committee selected to assess the study was specifically configured to assess studies recruiting patients who lack capacity. Consent procedures for this emergency study follow the recommendations of consumer groups and the Royal Colleges and are in compliance with ethical and regulatory frameworks. Women who bleed after childbirth and meet the eligibility criteria are randomised into the trial in the emergency situation where treatment needs to be given urgently and there is no time for prior consent.

We discussed the use of placebo injections with consumers, and these discussions supported our study design. There was a clear consumer preference for placebo injections, which increased the reliability of the answer to the research question. The approaches undertaken are compliant with the required regulations and national guidelines and fully justifiable.

Protocol amendments are submitted to the required regulators and sent to investigators following approval. If applicable, participants are made aware of protocol amendments.

Every care will be taken in the course of this research study. However, in the unlikely event that participants are injured as a result of the managing organisation (University of Liverpool), compensation may be available.

The TMG will form the basis of the Writing Committee and advise on the nature of publications. The Uniform Requirements for Manuscripts Submitted to Biomedical Journals will be respected. The results of the study will be disseminated via peer-reviewed publications. Requests for anonymised datasets can be sent to the chief investigator and sponsor following the publication of the trial results. The Standard Protocol Items: Recommendations for Interventional Trials reporting guidelines were used for drafting this manuscript.^27^

